## Abstract

**Background:**

The autonomic nervous system can be responsible for the initiation and maintenance of arrhythmias. Low-level tragus stimulation (LLTS), a noninvasive form of autonomic neuromodulation, has been shown to be effective in treating atrial fibrillation. We intended to treat frequent premature ventricular complexes (PVCs) with LLTS.

**Methods and design:**

The present study will be a prospective multicenter, double-blind, randomized, controlled trial to assess the antiarrhythmic effects of LLTS on frequent PVCs in patients without structured heart disease (SHD). A total of 100 patients with PVC burden > 10% will be randomly assigned to the active or sham LLTS in 1:1 fashion and receive the proposed intervention for 6 months. The primary outcome is PVC burden at 6 months as assessed by 10 days of continuous ambulatory electrocardiographic monitoring. Secondary outcomes include heart rate variability (HRV), quality of life, skin sympathetic nerve activity, and inflammatory markers. Adverse events will also be recorded.

**Discussion:**

The present trial will be the first to evaluate the effect of LLTS on frequent PVCs on patients without SHD. LLTS may serve as a low-cost, minimal-risk, and non-invasive alternative to conventional antiarrhythmic therapy.

**Trial registration:**

ClinicalTrial.gov NCT04909528. Registered on 17 June 2021. World health organization trial registration data set was shown in Supplementary Table 1.

**Supplementary Information:**

The online version contains supplementary material available at 10.1186/s13063-023-07713-2.

## Background

Premature ventricular complexes (PVCs) are the most common arrhythmias in clinical practice with an estimated prevalence of 1 to 4% in the general population on standard 12-lead electrocardiography and 40–75% of healthy individuals assessed by 24-h and 48-h ambulatory monitoring [1, 2]. The general impression is that PVCs in patients without structural heart disease (SHD) are benign [2, 3]. However, studies consistently demonstrated that PVCs could trigger malignant ventricular arrhythmias or even sudden cardiac death, especially in patients suffered from myocardial infarction (MI) [4, 5]. Additionally, frequent PVCs may be the primary etiology for PVC-induced cardiomyopathy [6] and lead to worsening of left ventricular dysfunction in patients with pre-existing cardiomyopathy [7].

Pharmacological therapies, including β-blockers and calcium channel blockers, are often prescribed as first-line treatment for patients with symptomatic or frequent PVCs [8, 9]. However, β-blockers or calcium channel blockers alone or their combination offer relief in less than 25% patients [10, 11]. Medical therapy may be discontinued due to lack of efficacy or intolerable side effects. Catheter ablation has also been recommended as first-line therapy for PVCs but can sometimes be challenging because of the anatomical obstacles [8, 9]. The other concern with this invasive approach is the rare but severe complications including aortic dissection, atrioventricular block, myocardial infarction, cardiac tamponade, and stroke [12].

Recent evidence suggests that the autonomic system can be responsible for arrhythmogenesis and arrhythmia maintenance. Invasive approaches, such as stellate ganglion block and cardiac sympathetic denervation, have shown antiarrhythmic effects in patients with refractory ventricular arrhythmias (VA) [13–15]. Continuous vagal stimulation reduced VA and prevented sudden cardiac death in a canine model of post-myocardial infarction [16]. It is widely accepted that increased cardiac sympathetic activity plays an important role in the generation of VAs; suppression of cardiac sympathetic tone and/or stimulation of cardiac parasympathetic tone may have antiarrhythmic effects on VAs. Low-level tragus stimulation (LLTS) targets the auricular branch of the vagus nerve, an afferent nerve that relays information to central vagal projections in the brain stem. The signal is processed in the brain stem and higher centers, which in turn provide the efferent neural signal to the heart, which reaches the target organ via the vagus nerve. In addition to the scientific basis for the antiarrhythmic effect, previous clinical trials have supported that LLTS is a non-invasive and safe alternative for the treatment of atrial fibrillation [17, 18]. There have been at least two animal models have demonstrated the antiarrhythmic effect of LLTS on VAs induced by MI [19, 20]. Currently, the chronic effects of LLTS on VAs in humans remain unknown. Therefore, we designed a multicenter, double-blind, randomized, controlled trial between an LLTS group and a sham-control group, both receiving standard antiarrhythmic drug treatment, to: (1) assess the antiarrhythmic effects of LLTS on frequent PVCs in patients without SHD, (2) explore the possible mechanism of LLTS responsible for its antiarrhythmic effects, and (3) identify the potential responders to this novel therapeutic strategy.

## Methods/design

### Study design

The transcutaneous electrical vagus nerve stimulation to suppress premature ventricular complexes (TREAT PVC) trial is a prospective, multicenter, double-blind, sham-controlled, randomized clinical trial (ClinicalTrials.gov Identifier: NCT04909528). The design of the TREAT PVC trial is summarized in Fig. 1. Briefly, all eligible subjects who have given informed consent will be randomly assigned to active or sham LLTS in a 1:1 fashion and will receive the proposed intervention for 6 months. Primary and secondary outcomes will be measured at 3 and 6 months. The timetable for enrolment, intervention, and assessments is shown in Fig. 2.

**Fig. 1 Fig1:**
[figure not shown]
Flowchart of the prospective trial. LLTS indicates low-level tragus stimulation, PVC premature ventricular complexes

**Fig. 2 Fig2:**
[figure not shown]
Time schedule of enrolment, interventions, assessments and visits for participants. EKG indicates electrocardiogram, LLTS low-level tragus stimulation, SKNA skin sympathetic nerve activity

### Participants and eligibility criteria

#### Inclusion criteria

Age of 18 to 80 yearsSymptomatic PVCs refractory to ≥ 1 antiarrhythmic drugs (including β-blockers and calcium-channel blockers)PVC burden ≥ 10%Arrhythmias originated from any focus (foci) in the right ventricular or left ventricular

#### Exclusion criteria

Ejection fraction (EF) < 45% unless proven to be PVC-mediated cardiomyopathy (history of improving LVEF by > 15% when PVC burden was reduced by pharmacological agents or ablation)EF continues to decrease in the past 4 months regardless of the etiologyUnwilling to continue current pharmacological therapy during the study period (6 months)Severe heart failure with NYHA Class ≥ IIIVAs attributed to underlying structural heart disease, known myocardial scar or myocarditisChange the dosing of antiarrhythmic drug, including β-blockers and calcium channel blockers, within 2 months prior to enrollmentUnsuccessful ablation within 3 months before recruitmentPatients are on amiodaronePatients with known thyroid issues or renal dialysisLife expectancy of < 12 months.

### Recruitment and enrollment

Recruitment will be conducted through the electrophysiology clinic of the First Affiliated Hospital of Nanjing Medical University and all other participating hospitals. Consecutive patients with frequent PVC will be screened for eligibility and approached for participation in the study. In addition, an investigator-handbook and training events will be conducted for referring physicians in the study to achieve adequate participant enrolment. Specifically, we will identify those patients who have a PVC burden of at least 10% measured by 24-h holter after correcting for some common reversible causes for PVC, such as caffeine intake, electrolyte imbalance, and staying up late. For patients who agree to consider participation, a member of the study team will describe the potential risks/benefits, outline the study interventions, and conduct recruitment assessments. For willing and eligible patients, we offer a 10-day single-lead electrocardiogram (ECG) patch monitor to accurately determine their PVC burden.

### Randomization and blinding

After baseline measurements have been collected, patients will be randomized 1:1 to active or sham LLTS using a central computerized randomization system to ensure blocked randomization. Sequence generation will be performed by an independent researcher through R, with a 1:1 allocation. To guarantee allocation concealment and to avoid selection bias, an independent researcher not involved in the trial will be charged to the custody of the sequences generated and to the allocation of the participants to each condition. Patients will not be informed of which stimulation site (tragus vs. earlobe) provides active stimulation. The investigators who assess the outcomes are also blinded to treatment allocation. The research coordinators who instruct the participant on ear clip placement according to randomized assignment and the study statistician are unblinded.

Unblinding can be performed at any time if participants experience an emergency. If necessary to ensure adequate treatment, where the principal investigator deems it necessary to identify the treatment, the investigator may perform unblinding and record the breach of blinding.

### Study intervention

#### Intervention description

For the patients allocated to the active stimulation groups, LLTS is delivered through a transcutaneous electrical nerve stimulation device (Parasym device, Parasym Health, Inc, London, UK) by attaching an ear clip to the tragus, which is innervated by the auricular branch of the vagus nerve (Fig. 3). In the sham group, stimulation was delivered to the earlobe, which is devoid of vagal innervation. Subjects in both groups are instructed to stimulate the tragus or earlobe twice a day for half an hour each time. The left and right tragi/earlobes will be stimulated alternatively. The device is set to a pulse width of 200 μs and a pulse frequency of 20 Hz, while the stimulation intensity is individually titrated to an amplitude above the threshold of perception and 1 mA below the level of discomfort.

**Fig. 3 Fig3:**
[figure not shown]
Real photo of how LLTS is applied

#### Criteria for discontinuing or modifying allocated interventions

As a non-invasive treatment, LLTS carries a very low risk of potential harm. Adverse events may include, but are not limited to, hypotension, bradycardia, fainting, severe pain, and local infection. All adverse events and their management will be recorded from baseline to 6 months. Circumstances in which individual participants may discontinue or modify the intervention include the occurrence of intolerable or unexpected side effects during the course of the therapy, and other circumstances that would endanger participant’s health if they continued in the study, as well as at participant request.

#### Relevant concomitant care and interventions permitted or prohibited during the trial

During the trial period, existing drug therapy will be continued with minimal changes possible. A change of medication during the treatment is not prohibited, but will be recorded as an event that requires additional modification.

### Follow-up schedule

The planned follow-up period is 6 months, and two outpatient visits are scheduled at 3 and 6 months over this treatment duration. The assessments performed at each visit are displayed in Fig. 4.

**Fig. 4 Fig4:**
[figure not shown]
Schedule of enrollment, intervention, and assessments (SPIRIT figure). Patients with frequent PVC were randomized into sham (no chronic LLTS) and active (chronic LLTS) groups. Ten days of continuous ECG monitoring at baseline and 3 and 6 months was performed to calculate PVC burden before and after LLTS treatment. In addition, 1 min of ECG, treatment compliance, 36SF questionnaire, SKNA, and blood samples were collected at baseline and 3- and 6-month follow-up visits. ECG indicates electrocardiogram, LLTS low-level tragus stimulation, PVC premature ventricular complexes, SKNA skin sympathetic nerve activity

### Primary outcome measures

#### PVC burden

At baseline and 3 and 6 months, patients will receive 10 days of continuous ECG monitoring to evaluate their PVC burden (reported as the percentage of all recorded beats that are PVCs throughout the study) using an adhesive ECG patch monitor (CardioGuard, Zhengxin Information Technology Co. Ltd., Shanxi, China). The P waves and QRS complexes were automatically classified and manually verified as normal sinus rhythm, premature atrial complexes or PVCs, or noise by comparison with adjacent waves. Each QRS complex in episodes of non-sustained ventricular tachycardia will be counted as a PVC. The mean PVC burden at each time point will be used to test the antiarrhythmic effect of LLTS on PVCs.

### Secondary outcomes measures

#### Heart rate variability (HRV)

HRV will be generated while monitoring PVC burden with the monitor patch to quantitatively evaluate the balance between the sympathetic and vagal nerves at baseline and 3 and 6 months. The R-R intervals will be derived from the adjacent normal sinus beats (i.e., N–N intervals). Time domain measurements, including SDNN, SDNN index, root mean square of successive R-R interval differences (RMSSD), the proportion of NN50 (the number of pairs of successive R-R intervals that differ by more than 50 ms) divided by the total number of R-R intervals (pNN50) will be calculated automatically. The power spectrum including very low frequency (LF) power (0.01–0.05 Hz), LF power (0.05–0.15 Hz), and high frequency (HF) power (0.15–0.5 Hz) will be estimated by Welch’s averaged periodogram method. The LF/HF ratio will also be calculated and considered an index of sympathetic–parasympathetic balance. The means of these HRV parameters will be used to determine the effect of LLTS on autonomic nervous system.

#### Treatment compliance

Patients will be requested to keep a daily log of the time and duration of LLTS application, amplitude settings, and any discomfort associated with each daily session. The cumulative number of stimulation hours recorded by the stimulator will be correlated with the daily log as an objective measure of compliance to the stimulation protocol.

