### Sample size calculation

Based on the 11 patients who underwent 1 month of stimulation, the average burden at baseline was 21.7% and the relative reduction after stimulation was 16.4%. We assume a baseline burden of 15% and expect a reduction of 40% at the end of 6 months. A sample size of 90 patients would provide at least 80% power to detect the specified effect sizes at a two-sided significance alpha level of 0.05. The sample size was calculated by using online statistic system (STATBOX, http://www.cnstat.org/statbox/; last access 9/19/2023). The exact formula used for sample size was as follows.$$1-{\varvec{\beta}}={\varvec{P}}{\varvec{\upgamma}}[{\varvec{F}}(1,{\varvec{N}}-2,{\varvec{N}}\{\left({{\varvec{\upomega}}}_{1}{{\varvec{\upomega}}}_{2}\right)[\frac{{{\varvec{\mu}}}_{1}-{{\varvec{\mu}}}_{2}}{{\varvec{\sigma}}}{]}^{2}\})\ge {{\varvec{F}}}_{\boldsymbol{\alpha }}]$$$${{\varvec{n}}}_{1}={{\varvec{N}}}^{\boldsymbol{*}}{{\varvec{\omega}}}_{1},\boldsymbol{ }{{\varvec{n}}}_{2}=\boldsymbol{ }{{\varvec{N}}}^{\boldsymbol{*}}{{\varvec{\omega}}}_{2}$$

To account for a potential drop-out rate of 10%, 50 patients in each group and 100 patients in total are planned to be recruited.

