## Discussion

### Significance

TREAT PVC trial will contribute to the current literature at multiple levels. Clinically, it will be the first study to investigate whether LLTS can reduce the PVC burden in patients without SHD who suffer from frequent PVCs. LLTS may turn out to be a low-cost, minimal-risk, non-invasive alternative to antiarrhythmic or ablative treatment for these patients. Scientifically, the trial may shed new light on the mechanisms underlying the antiarrhythmic effects of LLTS. Previous literature supported the hypothesis that the antiarrhythmic effect of LLTS was attributed to its anti-adrenergic and possibly anti-inflammatory effects [17, 18]. To corroborate these hypotheses, we will collect data such as skin sympathetic nerve activity, heart rate variability, and inflammatory markers, such as interleukin-1β, interleukin-6, and tumor necrosis factor-α at baseline and during the treatment course, which may help elucidate the underlying antiarrhythmic mechanism. Additionally, these measurements will also help to clarify the correlation between autonomic perturbance and ventricular arrhythmias. Last but not least, these data will also help us to identify the responders to this neural therapy.

From the perspective of patients, the trial focuses not only on PVC burden but also on patients’ adherence and quality of life. As patient compliance is of paramount importance for the efficacy of the self-administrated treatment, it will be highly valuable to include the patients’ perspective in the development and evaluation of the intervention. A diary log and the SF-36 questionnaire will be introduced to assess the degree to which patients feel symptomatically improved by the intervention.

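### Compliance is to be measured by correlating stimulator hours with the patient's log, a statistic that cannot show how much of the prescribed stimulation was delivered

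*Protocol article*

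**What the plan says.** The protocol article places Treatment compliance among the secondary outcome measures. Two records are kept. One is self-reported: "Patients will be requested to keep a daily log of the time and duration of LLTS application, amplitude settings, and any discomfort". The other is the running total of hours stored by the stimulator. The section then states how they are to be used: "The cumulative number of stimulation hours recorded by the stimulator will be correlated with the daily log as an objective measure of compliance", where compliance means compliance to the stimulation protocol.

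That stimulation protocol is set in Intervention description: "Subjects in both groups are instructed to stimulate the tragus or earlobe twice a day for half an hour each time". Follow-up schedule gives the duration: "The planned follow-up period is 6 months". No other section sets the recorded hours against this prescribed amount or defines compliance in another way. The Statistical plan contains no compliance analysis. In the Discussion, under Significance, the article says that "patient compliance is of paramount importance for the efficacy of the self-administrated treatment".

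**The concern.** Compliance is the amount of treatment delivered relative to the amount prescribed. The stated statistic compares delivered hours with reported hours and leaves prescribed hours out. A Spearman coefficient would show whether patients fall in the same order on the two records; a Pearson coefficient would show whether the records vary together linearly. Neither shows the level of use or whether the records agree. A coefficient is also one number for a group, so it gives no patient-level value to compare between arms or to relate to response.

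This matters because stimulation is self-administered at home for 6 months. If the trial is null, the reader will need to know whether stimulation failed or was not used. Identifying responders is one of the three aims in the Background, and low exposure is an obvious explanation for non-response.

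**Working it through.** The article states no compliance figure, so there is none to reproduce. The check is whether the stated statistic follows adherence.

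**Prescribed hours (from the article).** 2 sessions × 0.5 h = 1 h per day. Six months is taken as 180 to 183 days, which gives 180 to 183 h; at 3 months the figure is about 90 h.

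**Proportional over-reporting.** If every log equals 1.5 times the device hours, the correlation is exactly 1, whether patients did 30% or 100% of the sessions.

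**Constant over-reporting (assumed inputs).** Device hours have mean 110 and SD 30, limited to 0–180 h. Each log equals the device hours plus 40 h plus random error with SD 10 h.
- Correlation: 30/√(30² + 10²) = 30/31.6 = 0.95
- Device compliance: 110/180 = 61%
- Log-based compliance: (110 + 40)/180 = 83%

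Simulating 100 patients 4,000 times gives the same rounded values. Some simulated logs exceed 180 h; when logs are capped there, the correlation is 0.92 and log-based compliance 82%, so the result does not depend on impossible log entries.

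**Does the correlation rise with adherence?** Here the log error is assumed to have SD 3% of prescribed hours. Ignoring the limits at 0 and 100%, and with logs that are not proportionally inflated, r = s/√(s² + 3²), where s is the between-patient SD of device use in percentage points. Mean adherence does not appear in the formula.

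| Assumed mean adherence | Assumed SD | Log | r by formula | Pearson r, simulated |
|---|---|---|---|---|
| 30% | 15 | accurate | 15/√234 = 0.98 | 0.98 |
| 30% | 15 | overstated by 30 points (log mean 60%) | 0.98 | 0.98 |
| 70% | 15 | accurate | 0.98 | 0.98 |
| 95% | 2 | accurate | 2/√13 = 0.55 | 0.55 |
| 30% | 15 | unrelated to use | 0 | 0.00 |

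The simulated values are means over 1,000 runs of 100 patients, with 182 prescribed hours. Spearman coefficients were within about 0.02 of the Pearson values. The statistic is the same at 30% and 70% adherence, does not react to a uniform overstatement, and is much lower in the trial where nearly every session was done, because patients there hardly differ.

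**The alternative on the same cases.** Device hours divided by prescribed hours returns 30%, 30%, 70%, 95% and 30%. In the constant over-reporting example, the log-minus-device difference has mean 40 h and limits of agreement 40 ± 1.96 × 10, or about 20 to 60 h. That exposes the over-reporting which the correlation hides.

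**The case against.** The strongest reply is that one loose sentence is being read as a fixed analysis. No coefficient, unit of analysis or threshold is given, and the Statistical plan lists no correlation of these records. In clinical prose, correlating two records can mean checking one against the other. The word objective fits the device hours better than a comparison with a self-report, so the device hours may be the intended measure and the log only a check. The denominator is fixed elsewhere in the article, both records are kept for each patient, and summaries by arm and visit are detail that an article commonly leaves to the analysis plan.

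Much of this stands. The reading as a cross-check is possible, no information is lost, and the absence of by-arm summaries would not by itself be a finding. But correlation is the only method stated, and even as a cross-check it misses systematic over-reporting, the error to be expected in a self-kept log. The point is therefore that a stated method is unsuited to its purpose, not that detail is missing.

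A reader might go further and infer that the plan would declare a poorly adherent trial compliant. The article does not support that: it has no rule that turns a coefficient into a verdict, and logs unrelated to true use would give a correlation near zero. Nor should a reader infer that delivered exposure will be unknown, since the stimulator records it, or that the efficacy result is compromised. The abstract's list of secondary outcomes does not include compliance, and no test or decision is tied to it.

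**Conclusion.** The point holds in limited form. The correlation named as the measure of compliance cannot show how much stimulation was delivered, can be high when adherence is poor, and can be low when adherence is uniformly good. That conclusion is a property of the statistic and needs no assumption about this trial. The sizes shown (0.95 with 61% device compliance; 0.98 at both 30% and 70%; 0.55 at 95%) rest on assumed adherence, spread and log error. They illustrate the mechanism and do not forecast what these patients will do.

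The damage is confined to the compliance outcome and to the interpretation of the main result. It is worth correcting because the article itself gives compliance such weight and the better measure is already being recorded.

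**What to change.** In Treatment compliance, replace the correlation with a per-patient measure: device-recorded hours divided by prescribed hours to date (about 90 h at the 3-month visit and 180 h at the 6-month visit, adjusted to the actual visit dates). Summarise it by arm and visit. Keep the log for timing, amplitude and discomfort and as a cross-check on the device, reported as the mean difference between log and device hours with limits of agreement.

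The cost is a change of wording in the protocol or analysis plan. No new data, visits or patients are needed, and neither the treatment nor the primary analysis changes.
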